### Experimental set-up and procedures

To perform tensiomyographic measurements, we will use a TMG-S1 electrical stimulator (TMG-BMC d.o.o., Ljubljana, Slovenia), a GD30 displacement sensor (Panoptik d.o.o., Ljubljana, Slovenia) and two squared self-adhesive electrodes (50x50 mm, Axion GmbH, Leonberg, Germany). The signal of the displacement sensor will be recorded using the TMG Software v3.6 (TMG-BMC d.o.o., Ljubljana, Slovenia).

All measurements will be performed on the RF and BF of the dominant leg. The dominant leg will be the leg that subjects reportedly would use to shoot a ball on a target [44]. The RF measurements will be performed with subjects lying in a supine position, with their arms rested aside and the knee supported at an angle of approximately 120° by a triangular foam pad provided by the manufacturer [31]. The BF measurements will be performed with subjects lying in a prone position, with their arms rested aside and the ankle supported by a semicircular foam pad, creating a knee angle of approximately 175° flexion [28]. For both muscles, 180° corresponds to full knee extension, respectively.

The skin in the area of measurement will be cleaned with alcohol-soaked gauze before the positioning of the sensor and the electrodes. The position of the sensor will be determined in three steps: First, the midpoint on a line between the superior border of the patella and the anterior superior iliac spine for the RF and the BF, the midpoint on a line between the fibula head and ischial tuberosity will be determined, according to [45]. Second, the thickest part of the muscle belly in the area of the point determined during the first step will be identified by inspection and palpation during a voluntary contraction. Third, if necessary, the sensor position will be adjusted at the beginning of the progressive stimulation to obtain the highest radial displacement [26, 27]. Once the position of the sensor is identified, we will place the electrodes at a distance of 7 cm from each other, measured between the facing edges of the two electrodes, and a distance of 3.5 cm between the sensor and the proximal and distal electrodes, respectively [46]. The position of the sensor and electrodes will be marked using a dermatological pen to ensure consistent positioning during this study.

The electrical stimulation will consist of single, monophasic, square wave stimuli with a duration of 1 ms each to elicit single isometric twitches. The stimulation will start at an initial stimulation amplitude of 30 mA, and will be then increased in steps of 10 mA. During M1, M2 and M3, we will apply progressive electrical stimuli with rest-intervals of 15 s between consecutive stimuli to obtain the individual maximal displacement. The stimulation amplitude will be increased until there is no further increase of the maximum radial displacement or until the stimulator’s maximum output (110 mA) is reached. During the three blocks of repeated stimulation at 50 mA on the second day, the rest intervals between consecutive stimuli will be 10 s, 20 s and 30 s, respectively.

From M1, M2 and M3, the two displacement curves with the highest radial displacement of each measurement will be averaged respectively and used for further analysis. From block 1, block 2 and block 3, we will use every single displacement curve for further analysis.

### Rate of displacement calculation formulas

Fig 2 illustrates three generic tensiomyographic parameters and the five different approaches to calculate Vc from the displacement curve. The TMG software will automatically calculate the following parameters (Fig 2A): maximum radial displacement (Dm, mm), delay time, which refers to the time interval between the stimulus and 10% of Dm (Td, ms) and contraction time, which refers to the time interval between 10% and 90% of Dm (Tc, ms).

**Fig 2 pone.0262156.g002:**
[figure not shown]
Typical displacement curve during the twitch contraction phase until maximum displacement and tensiomyographic parameters. (A) Three generic tensiomyographic parameters: maximum radial displacement (Dm), Delay time (Td), Contraction time (Tc). (B) Mean rate of displacement from electrical stimulus until 10% of Dm (Vc_0-10%_), mean rate of displacement from electrical stimulus until 90% of Dm (Vc_0-90%_) and mean rate of displacement between 10% and 90% of Dm (Vc_10-90%_).

From these data, we will calculate (1) the mean rate of displacement during the time interval between the electrical stimulus until 10% of Dm as Vc_0-10%_ = 0.1 * Dm / Td (mm/s) [17] (Fig 2B), (2) the mean rate of displacement during the time interval between the electrical stimulus until 90% of Dm as Vc_0-90%_ = 0.9 * Dm / (Td + Tc) (mm/s) [25] (Fig 2B), (3) the mean rate of displacement during 10% and 90% of Dm as Vc_10-90%_ = 0.8 * Dm / Tc (mm/s) [17] (Fig 2B), (4) the normalized rate of displacement by dividing the mean rate of displacement during 10% and 90% of Dm by Dm as Vc_norm_ = 0.8 / Tc (1/s) [30] and (5) the ratio of Dm and the time interval from the stimulus until 90% of Dm as Vc_Dm/t90%_ = Dm / (Td + Tc) (mm/s) [29] (Fig 2A).

### Statistical analysis

We will report Vc_0-10%_, Vc_0-90%_, Vc_10-90%_, Vc_norm_ and Vc_Dm/t90%_ for both the RF and BF descriptively as mean (M) and standard deviation (SD). All data will be checked for outliers via visual inspection of boxplots. Outliers will be defined as data points outside of three times the interquartile range. The normal distribution of all variables will be tested using the Shapiro-Wilk Test. To assess a systematic bias between M1-M2 and M1-M3, we will perform a two-tailed paired t-test, respectively [47].

For the assessment of relative reliability, we will calculate intra-class correlation coefficients (ICC, mean rating (k = 2), absolute agreement, two-way mixed-effects model) with 95% confidence intervals (CI) [48]. ICC scores lower than 0.5, between 0.5 and 0.75, between 0.75 and 0.9 or greater than 0.9 will be interpreted as poor, moderate, good or excellent reliability [48].

Absolute reliability will be quantified by calculating the standard error of measurement (SEM and SEM%), the minimal detectable change (MDC and MDC%) [49] and the CV [47], including the respective 95% CI’s. The SEM indicates the estimation precision of a measure and will be calculated as SEM = SD * √1-ICC [47]. The SEM% allows a comparison of different Vc calculations as it is unitless and will be calculated as SEM% = (SEM / M)* 100 [50]. The MDC presents the smallest difference between two measures that can be differentiated from measurement error and hence may be considered real [49]. Following Weir et al. [49], we will calculate the MDC as MDC = SEM * 1.96 * √2. The MDC% will be calculated as MDC% = (MDC/M) * 100 [50] to allow a comparison between different calculations of Vc independently of units. The CV will be calculated as CV = SD / M * 100 [47], whereby SD refers to the standard deviation and M to the mean of individual differences between M1 and M2 or M1 and M3. A CV > 10% will be interpreted as insufficient reliability with reference to previous studies investigating the reliability of tensiomyographic parameters [27, 51, 52].

To assess the effects of different ISI on Vc during repeated stimulation, we will employ a within-subject repeated-measures ANOVA. The two independent variables will be ISI (10 s, 20 s, 30 s) and stimulus number (stimulus 1 to stimulus 10). The dependent variables will be Vc_0-10%_, Vc_0-90%_, Vc_10-90%_, Vc_norm_ and Vc_Dm/t90%_ for both the RF and BF, respectively. Pairwise comparisons with Bonferroni correction will applied for significant main effects. The effect size Cohen’s d will be calculated as d = M_diff_ / √SD_1_ + SD_2_ / 2 [53] for pairwise comparisons to allow comparisons between effects of different ISI and between consecutive stimuli. Thresholds for small, moderate, large, very large or extremely large effects will be 0.2, 0.6, 1.2, 2.0 and 4.0 [54].

Statistical significance will be set at alpha ≤ 0.05. Missing data will be handled by listwise deletion of cases with missing data [55]. All statistical analyses will be performed using R studio and respective packages. Upon completion of the data collection and analysis, the raw data disaggregated by sex and the analysis code will be openly available at https://osf.io/4du2j/?view_only=ee7a4afb30514cb9a2e15381282dcec8.

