### Sample size justification

Two different calculations were made to justify the sample size for this study. First, a precision-based calculation for the ICC of Vc was based on previous reliability studies [27, 28]. For this calculation, we used RStudio, Version 1.3.959 and the "Nest"-function from the "ICC" package version 2.3.0 [40]. Assuming the lowest ICC reported of 0.92 [28], two measurements per subject and an alpha level of 0.05, we will need 18 subjects to achieve the desired precision with a confidence interval of 0.15.

Second, to estimate how many subjects we will need to detect an effect of changing the interstimulus-interval on Vc, we used the raw data provided by Wilson et al. [31]. From those data, we calculated Vc_10-90%_ = 0.8 Dm / Tc and Vc_norm_ = 0.8 / Tc (S1 Table). As only Dm and Tc were included in those raw data, we could not apply the other three formulas. We performed a two-way (ISI x measure) repeated measures analysis of variance (ANOVA) to estimate the main effect of inter-stimulus interval on Vc_10-90%_ and Vc_norm_. We obtained effect sizes using RStudio and the "eta2_to_f"-function from the "effectsize" package [41] and calculated the sample size using the "wp.rmanova"-function from the "WebPower"-package [42]. For the sample size calculation, we assumed three groups, ten measurements per subject, an effect size f = 3.1 (Vc_10-90%_) and f = 1.6 (Vc_norm_), a nonsphericity correction coefficient of 0.7 (Vc_10-90%_) and 0.6 (Vc_norm_), an alpha level of 0.01, a power of 0.95 and a between effect, a total of 9 (Vc_10-90%_) subjects and 18 (Vc_norm_) subjects were needed. We confirmed the estimated sample size for the ANOVA by repeating the calculations for both Vc_10-90%_ and Vc_norm_ using g*power v3.1.9.2 [43]. Based on the results of both calculations for the ICC and the ANOVA and accounting for potential dropouts, we intend to recruit 24 subjects.

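### The ICC reliability classes make no use of the planned 95% confidence intervals, so the good/excellent label is unstable when the true ICC lies near 0.90

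*Protocol article*

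**What the plan says.** All references are to the protocol article.

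- **Statistical analysis.** Relative reliability is measured by a mean-rating (k = 2), absolute-agreement, two-way mixed-effects ICC with a 95% CI. ICC scores below 0.5, from 0.5 to 0.75, from 0.75 to 0.9 and above 0.9 "will be interpreted as poor, moderate, good or excellent reliability". Nothing is said about an interval that crosses a limit. SEM, MDC and CV are also planned with 95% CIs, and SEM% and MDC% are named as the unit-free measures for comparing formulas.
- **Sample size justification.** The precision calculation reads "Assuming the lowest ICC reported of 0.92", with "two measurements per subject and an alpha level of 0.05", and concludes "we will need 18 subjects to achieve the desired precision with a confidence interval of 0.15". The target is then raised: "accounting for potential dropouts, we intend to recruit 24 subjects".
- **Introduction and Discussion.** The study is meant to compare five formulas directly on reproducibility and to help towards a standard approach. For two of the five, reproducibility is described as still unclear. Published results are summarised with the same excellent label at ICC above 0.90.

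**The concern.** The rule sorts each estimate into a verbal class as if it were known exactly, although an interval is planned for it. The limit that matters is 0.9, because the planning value and the cited results lie close to it. Labels will be assigned for five formulas, two muscles and two comparisons (within-day and between-day). If one formula is called good and another excellent, readers will take the second to be more reliable. Near 0.90 the two estimates may differ only by sampling error. In a study intended to guide the choice of formula, that contrast could support a preference that the data do not.

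**Working it through.** **1. The plan's own figure.** I take the planning function to use the Bonett width approximation for a single-measure ICC: n = 8z²(1−ρ)²[1+(k−1)ρ]² / [k(k−1)w²] + 1. With z = 1.96, ρ = 0.92, k = 2 and w = 0.15 this gives 17.11, rounded up to 18. The stated figure reproduces, with 0.15 as the total width; read as a half-width it would give 5.03, so 6 subjects. At n = 24 the same formula gives a width of 0.126.

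**2. From the planning scale to the labelled scale.** The labelled ICC is the mean of two measurements. A single-measure 0.92 corresponds to 2 × 0.92 / (1 + 0.92) = 0.958.

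**3. Intervals for the labelled ICC, n = 24.** I used the exact one-way F interval for k = 2, as an approximation to the two-way interval. Lower bound = 1 − 2.282 × (1 − ICC); upper bound = 1 − (1 − ICC) / 2.299. The constants are the 97.5% points of F(23, 24) and F(24, 23).

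| Observed mean-rating ICC | 95% CI | Label under the rule |
|---|---|---|
| 0.92 | 0.82 to 0.97 | excellent |
| 0.94 | 0.86 to 0.97 | excellent |
| 0.95 | 0.89 to 0.98 | excellent |
| 0.958 | 0.905 to 0.982 | excellent |

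The lower bound reaches 0.90 when 1 − ICC = 0.10 / 2.282 = 0.044, that is, at an observed value of about 0.956. Between 0.90 and that value the rule says excellent while the interval extends into good.

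**4. How often the label is excellent.** Simulation of the absolute-agreement, mean-rating ICC, with normal data and no systematic shift between sessions:

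| True mean-rating ICC | Called excellent, n = 24 | n = 18 |
|---|---|---|
| 0.85 | 17% | 20% |
| 0.87 | 26% | 29% |
| 0.88 | 33% | 35% |
| 0.90 | 50% | 50% |
| 0.92 | 70% | 68% |
| 0.93 | 80% | 77% |
| 0.95 | 95% | 92% |
| 0.958 | 98% | 96% |

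At n = 24 a true 0.92 therefore gets a lower class in 100 − 70 = 30% of studies, and a true 0.95 in 5%.

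**5. Two equally reliable formulas.** How often they receive different labels depends on the correlation between their estimates, which the document does not give. At a true 0.90 and n = 24, independent formulas would differ in 2 × 0.5 × 0.5 = 50% of studies. Simulation gives 28% at an assumed between-formula correlation of 0.8 and 14% at 0.95. At a true 0.958 the figure is about 2% to 4%. One pair can never differ: Vc_0-90% is exactly 0.9 times Vc_Dm/t90%, so both have the same ICC.

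**The case against.** Several points on the other side are sound.

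- **The planned width.** A reader might note that "the desired precision with a confidence interval of 0.15" matches the width of the good class (0.90 − 0.75 = 0.15) and infer that the labels are largely chance. The document does not support this. The 0.15 belongs to a single-measure ICC of 0.92 with 18 subjects. On the labelled scale the corresponding value is 0.958, and with 24 subjects its interval is 0.982 − 0.905 = 0.077 wide and lies wholly inside excellent. There the label is obtained in about 98% of studies. Two limits apply: the article does not say whether the published 0.92 is a single-measure or a mean-rating value (if the latter, the 30% error applies), and two formulas have no published reliability data.
- **Any cut-off is unstable beside the cut.** True, but the rule can acknowledge this at no cost, because the intervals are already planned.
- **The labels are not the only evidence.** This stands. SEM% and MDC% are the stated tools for comparing formulas, and all intervals will be visible. It would be wrong to treat the labels as the sole basis of the comparison.
- **The formulas share the same curves.** This stands too. It reduces false contrasts between labels, by an amount that cannot be fixed from the document.
- **The wording does not say point estimate.** Correct, but that is the natural reading of a rule applied to scores, and no role for the bounds is stated.
- **The CV limit.** A reader might extend the point to "A CV > 10% will be interpreted as insufficient reliability". No sampling error or misclassification rate has been worked out for the CV, so that extension is not made here.

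**Conclusion.** The point holds in a limited form. The classification rule leaves out the intervals that the same paragraph plans, and with 24 subjects the good/excellent label is unreliable for true mean-rating ICCs of roughly 0.87 to 0.93. Outside that range, and at the plan's own planning value converted to the mean-rating scale, it is dependable. The sample size calculation is not in error. The figures assume normal data, no session shift, 24 subjects completing and, for the intervals, the one-way approximation. With 18 completers the intervals are somewhat wider: an observed 0.92 has a CI of 0.79 to 0.97. This is a cheap improvement to the interpretation rule, and it changes no estimate.

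**What to change.** In the Statistical analysis section, replace the classification sentence with a rule tied to the 95% CI:

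- report every class that the interval spans, for example good to excellent;
- use a single label only when the whole interval lies in that class;
- state that a difference in label between formulas will not be read as a difference in reliability.

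This needs no new data, subjects or analyses. The cost is fewer unqualified labels. With 24 subjects, plain excellent would need an observed ICC of about 0.956 or more. A formula whose true value is 0.958 would clear that bar in only about half of studies, and would otherwise mostly be reported as good to excellent.

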As a result, an increasing number of studies reports the rate of displacement (Vc), i.e. the slope of the radial displacement-time curve. Several different formulas exist to calculate Vc but no consensus exists on the most suitable formula. Further, there is a lack of studies investigating the reproducibility of these formulas, as only two studies investigated the reliability of Vc so far. Lohr et al. [27] investigated the within and between-day reliability of Vc in the lumbar erector spinae muscle of healthy females and males, using this formula: Vc = 0.8*Dm / Tc. Vc in this study showed an excellent relative (intraclass correlation coefficient ICC > 0.90) and absolute (coefficient of variation CV < 8%) reliability. De Paula Simola et al. [28] investigated the between-day reliability of the following two formulas to calculate Vc in twenty male sports students: V_10_ = 0.1*Dm / t_10%_ and V_90_ = 0.9*Dm / t_90%_ [28]. Absolute reliability was higher in rectus femoris (RF) and biceps femoris (BF) (CV < 10%) compared to gastrocnemius lateralis (CV = 12.3% and CV = 11.3% for V_10_ and V_90_, respectively) [28]. Both formulas showed excellent relative reliability in all three muscles (ICC > 0.90) [28]. In addition to the formulas used in the two studies mentioned, two other formulas to calculate Vc have been frequently reported: Vc = Dm / (Td +Tc) [29] and Vc_rn_ = 0.8 / Tc [30]. The reproducibility of Vc calculated by these two formulas is still unclear. Therefore, information on the reproducibility of these two formulas is needed. Further, a direct comparison of all five formulas for calculating Vc in terms of their reproducibility within the same sample would help reach a consensus on a standardized approach.

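### The CV is divided by the mean between-session difference, which should be near zero, so the 10% rule carries no information on reliability

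*Protocol article*

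**What the plan says.** The Statistical analysis section of the protocol article lists the CV with SEM and MDC as a measure of absolute reliability. It gives the formula, "The CV will be calculated as CV = SD / M * 100", and then its terms: "whereby SD refers to the standard deviation and M to the mean of individual differences between M1 and M2 or M1 and M3". It attaches a decision rule: "A CV > 10% will be interpreted as insufficient reliability with reference to previous studies" of tensiomyographic parameters.

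Three other statements bear on this:
- The same section uses M for something else in the descriptive statistics, where each Vc is reported "descriptively as mean (M) and standard deviation (SD").
- The same section examines the same differences for bias: "To assess a systematic bias between M1-M2 and M1-M3, we will perform a two-tailed paired t-test".
- The Introduction gives the scale of CVs in earlier work. One study of the erector spinae "showed an excellent relative (intraclass correlation coefficient ICC > 0.90) and absolute (coefficient of variation CV < 8%) reliability". In another, "Absolute reliability was higher in rectus femoris (RF) and biceps femoris (BF) (CV < 10"%), with 12.3% and 11.3% in the gastrocnemius lateralis.

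No other part of the article gives a different definition of the CV.

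**The concern.** A coefficient of variation relates measurement error to the size of the quantity measured. Here the divisor is the mean change between sessions, which a reproducible measure should bring close to zero. The ratio then has no upper bound, takes its sign from whichever session happened to be higher, and falls when systematic bias increases.

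Within- and between-day reliability of five Vc formulas is the study's first aim. Among the absolute-reliability indices, the CV is the only one with a pass/fail threshold. That verdict would rest on a number unrelated to the measurement error of Vc, and on a different scale from the earlier studies that supply the threshold. The analysis is to be preregistered with open code, so following the text gives an uninterpretable result and departing from it is an unplanned deviation.

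**Working it through.** The article reports no CV of its own to reproduce, so the check is of what the written definition does.

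**Inputs from the article.** n = 24 (Sample size justification); CV formula, meaning of M, 10% rule and paired t-test (Statistical analysis).

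**Assumptions not in the article, used only in steps 4 and 5.** Between-subject SD of 25% of the mean, within-subject CV of 3% to 10%, and a systematic shift of −5% to +10% of the mean; 100,000 simulated studies per setting.

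**Step 1: link to the paired t-test.** Take SD as that of the differences. Since t = mean_diff/(SD_diff/√n),

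|CV| = 100·SD_diff/|mean_diff| = 100·√n/|t|.

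With n = 24, 100·√24 = 489.9, so |CV| = 489.9/|t|. This CV is the bias test turned upside down.

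**Step 2: no systematic bias.** The statistic then follows a t distribution with 23 degrees of freedom whatever the measurement error. The median of |t| is 0.685, so the median |CV| is 489.9/0.685 ≈ 715%. The middle half runs from about 415% to 1,519%. The sign is negative in half of samples.

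**Step 3: what the threshold demands.** |CV| ≤ 10% needs |mean_diff| ≥ 10·SD_diff, that is |t| ≥ 10·√24 = 49.0. With no bias the probability is about 9 × 10⁻²⁵. A difference just significant at the two-sided 5% level (|t| = 2.07) still gives |CV| ≈ 237%. In terms of Vc, the required shift is 10·√2 times the within-subject CV: about 42%, 71% or 113% of the mean for within-subject CVs of 3%, 5% or 8%.

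**Step 4: direction of the index.** Simulated at a within-subject CV of 5%:

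| Systematic shift | Median \|CV\| as written | Share with signed CV above 10% |
|---|---|---|
| 0 | 714% | 0.50 |
| +2% | 348% | 0.92 |
| +5% | 140% | 1.00 |
| +10% | 70% | 1.00 |
| −5% | 140% | 0.00 |

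More bias makes the CV look better. With the sign kept, the +5% and −5% rows receive opposite verdicts, so the order of subtraction decides. In no simulated setting was |CV| ≤ 10%.

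**Step 5: the same rule with a mean of Vc as denominator, no bias.**

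| True within-subject CV | Median, SD_diff/(√2·mean) | Share above 10% | Median, SD_diff/mean | Share above 10% |
|---|---|---|---|---|
| 3% | 3.0% | 0.00 | 4.2% | 0.00 |
| 5% | 4.9% | 0.00 | 7.0% | 0.01 |
| 8% | 7.9% | 0.06 | 11.2% | 0.75 |
| 10% | 9.9% | 0.46 | 13.9% | 0.97 |

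Either form tracks the measurement error and lies on the scale of the cited CVs. They differ by √2, which at 8% puts the medians on opposite sides of the cut-off.

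**Other reading of SD.** The sentence can also be read with SD as that of the raw Vc values. The denominator is still the mean difference, so the ratio is just as unstable. With equal session variances and the ICC of 0.92 used in the sample size section, SD_diff = SD·√(2·0.08) = 0.4·SD, so the result would be 1/0.4 = 2.5 times as large.

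**The case against.** The best defence is that this is a slip of wording. M means the mean of Vc in the descriptive statistics, and SEM% and MDC% plainly need that sense. The 10% rule and the cited CVs fit a denominator on the scale of Vc. The reference to differences may have been meant for the SD only, and a CV of several hundred percent, or a negative one, would be noticed at once. This is plausible, and the source cited for the formula is not available to check it. It does not rescue the text: M is explicitly assigned to the differences, and the sentence does not show which conventional CV was meant. As step 5 shows, that choice can change the verdict.

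Two stronger readings are tempting, and the article does not support them.
- A reader might infer that the 10% rule would declare every formula insufficient. That holds only for the absolute value, which the article does not mention. Taken literally, a negative CV is not above 10% and passes, which with no bias happens about half the time.
- A reader might infer that the whole comparison of formulas is spoiled. It is not. The section assigns the unit-free comparison to SEM% and MDC%, and the ICC has its own interpretation bands. None of these uses the CV.

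It is also fair to say that recruitment, sample size, data collection and the inter-stimulus interval aim are untouched, and that the promised open data would let others recompute a CV.

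**Conclusion.** The definition is wrong as written; this is not a detail left to another document. At n = 24 with no systematic bias, the median |CV| is about 715% regardless of measurement error, its sign is arbitrary, and reaching 10% in magnitude would need a mean shift of at least 10 SDs of the differences. The 10% rule therefore carries no information on reliability, and the resulting CV cannot be compared with the cited range of below 8% to 12.3%.

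The no-bias figures rest only on n = 24, roughly normal differences and SD being that of the differences. The figures under bias and for the corrected CV also rest on the assumed error and shift sizes. With 18 subjects the conclusion is the same (median about 616%; |t| ≥ 42.4 needed).

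The damage is confined to the CV and its threshold. It should be corrected before analysis because the CV is the only absolute index with a cut-off and the correction is nearly free.

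**What to change.** Replace the sentence that defines SD and M for the CV:
- Define a within-subject CV whose denominator is the grand mean of the measured Vc values over the two sessions compared: CV = 100·SD_diff/(√2·grand mean). The log equivalent is 100·(exp(SD of ln-differences/√2) − 1). Name one form.
- Give the method for the promised 95% CI: chi-square distribution or bootstrap.
- Before applying the 10% cut-off, confirm from the studies cited for it whether their CV included the √2 divisor, and state which definition is used. If the definitions differ, the cut-off does not carry over unchanged.
- Use a separate symbol for the mean difference, so that M keeps one meaning throughout the section.

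The cost is a short text correction in the preregistered analysis section and one line of code, plus a look at the cited sources. Data collection does not change.

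### The three ISI pairs face both an omnibus test and a full Bonferroni correction; this is valid but needlessly conservative for a three-level factor

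*Protocol article*

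**What the plan says.** In the Statistical analysis section of the protocol article, the effect of ISI on the rate of displacement (Vc) is analysed as follows: "we will employ a within-subject repeated-measures ANOVA". The factors are ISI, with three levels (10 s, 20 s, 30 s), and stimulus number, with ten. The post-hoc rule is one sentence for both factors: "Pairwise comparisons with Bonferroni correction will applied for significant main effects". The significance level is also fixed there: "Statistical significance will be set at alpha ≤ 0.05".

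The analysis is run for five Vc formulas, "for both the RF and BF, respectively", which makes 5 × 2 = 10 ANOVAs. No adjustment across them is stated, and the section names no sphericity correction.

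Under Sample size justification, the planned number is given as: "accounting for potential dropouts, we intend to recruit 24 subjects". That section sizes the ISI main effect, not any pair, and assumes nonsphericity coefficients of 0.7 and 0.6.

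**The concern.** An ISI pair has to pass two hurdles. The ISI main effect must be significant, and the pair must then reach 0.05/3 = 0.0167. With three means, any two equalities imply the third. So once the global null is false, at most one of the three pairwise nulls can be true, and a correction for three comparisons is more than is needed at that stage.

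The second aim is to learn how different rest intervals affect Vc. A significant main effect says that some intervals differ, and the pairs say which. If the post-hoc rule is stricter than the error rate requires, a moderate difference between adjacent intervals (10 s versus 20 s, or 20 s versus 30 s) is more likely to be missed.

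**Working it through.** **The plan's own figures.** The protocol gives no power for a pairwise comparison, so there is none to reproduce. Its ANOVA sample sizes (9 and 18) concern the ISI effect treated as a between effect. With noncentrality f² × n × coefficient, 2 and n − 3 degrees of freedom, alpha 0.01 and power 0.95, I get n = 9 for f = 3.1 with 0.7, and n = 19 for f = 1.6 with 0.6 (power 0.940 at n = 18). These agree with the stated figures to within one participant. Nothing below changes them.

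**Inputs from the protocol.** n = 24, three ISI levels, alpha 0.05.

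**Assumptions.** Two-sided paired t-tests on each participant's block means; equal steps between intervals; sphericity unless stated; Greenhouse-Geisser-corrected omnibus test in the power simulations. Shifts are in SDs of the paired difference, and the range is mine because the documents give none.

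**Step 1: a single adjacent pair.** A 10–30 s shift of 1.0 gives an adjacent shift dz = 1.0/2 = 0.5. The noncentrality is dz × √24 = 0.5 × 4.90 = 2.45 on 23 degrees of freedom. Power is 0.461 at 0.05/3 and 0.650 at 0.05. The dz detectable with 80% power is 0.705 at 0.05/3 and 0.597 at 0.05.

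**Step 2: power with the omnibus test included** (20,000 to 40,000 simulated trials per scenario), adjacent pair:

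| 10–30 s shift | Plan | Shaffer | Omnibus, then each pair at 0.05 |
|---|---|---|---|
| 0.67 SD | 20% | 33% | 34% |
| 0.8 SD | 29% | 45% | 46% |
| 1.0 SD | 46% | 65% | 65% |

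For 10 s versus 30 s at 0.67 SD, power is 74% as planned and 80% with each pair at 0.05 after the omnibus test. After the same omnibus test, Shaffer rejects only a subset of what that rule rejects, so its gain for this pair is at most 80 − 74 = 6 points.

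Other patterns of means and nonsphericity shrink the gain. Over dz 0.4 to 0.7 for 10 s versus 20 s, testing each pair at 0.05 after the omnibus test gains about 1 to 19 points over the plan.

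**Step 3: why Shaffer keeps the error at 5%.**
- All three means equal: any rejection requires the smallest p-value to be at or below 0.05/3. By the Bonferroni inequality the error is at most 3 × 0.05/3 = 0.05.
- Exactly one pair equal: rejecting that pair requires its own p-value to be at or below 0.05, so the error is at most 0.05.
- Exactly two pairs equal cannot occur.

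Each paired t-test uses only its own differences, so sphericity plays no part. Keeping the omnibus precondition can only remove rejections. Every pair rejected under the plan is also rejected under Shaffer.

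**Step 4: familywise error of the other rules**, one outcome, n = 24:
- Plan: about 2–4% when all three means are equal, about 1.7% when one pair is equal.
- Greenhouse-Geisser omnibus test, then each pair at 0.05: about 5% in every configuration.
- Uncorrected omnibus test, then each pair at 0.05, under nonsphericity with all means equal: up to about 6.5%.

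**Step 5: the stimulus factor.** With ten levels, one differing and nine equal, an omnibus test followed by unadjusted pairs gives a familywise error of 0.60. Bonferroni over the 45 pairs gives 0.03.

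**The case against.** The strongest reply is that the planned rule is valid and conventional. It exceeds no error rate, contradicts nothing in the protocol and affects no stated sample size. All of that stands, and it is why the point is minor.

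The effect sizes behind the loss are also assumed. The protocol's own planning value f = 1.6, read as a within-subject effect with equal steps and sphericity, implies 48δ²/23 = 1.6², so an adjacent shift δ of about 1.1 SD. Power is then 99.6% with Bonferroni and 99.9% without, and the loss disappears. This stands too: the gain matters only if the true effects are moderate.

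One sentence has to serve both factors, and the ten-level factor does need adjustment. That limits the change to ISI but is no argument against it. Loosening the ISI tests also adds some false positives across ten unadjusted ANOVAs, which is a real but small cost.

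Three stronger readings are tempting, and the protocol does not support them:
- A reader might infer that 10 s versus 20 s is the key comparison. The Introduction hypothesises only that changing ISI affects Vc, and the sample size targets the main effect. The 10 s versus 20 s contrast appears separately only in a cited biceps brachii study.
- A reader might infer that the omnibus test alone controls the error, so that Bonferroni brings no benefit. That needs an omnibus test that is valid without sphericity. The Statistical analysis section names no correction, while the sample size section expects coefficients of 0.6 to 0.7. As written, Bonferroni does protect.
- A reader might infer that a missed pair will be taken as support for the short interval. The protocol does not say so, and it plans Cohen's d for the pairwise comparisons.

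**Conclusion.** The point holds as a modest matter of efficiency. For the three ISI pairs, an omnibus test plus full Bonferroni is valid but stricter than necessary. Under the stated assumptions, adjacent-pair power rises with Shaffer by about 13 points at a 10–30 s shift of 0.67 SD (33 − 20) and 19 points at 1.0 SD (65 − 46). The gain for 10 s versus 30 s is small, and for effects as large as the protocol's planning values it is practically nil. The error-rate argument for Shaffer does not depend on these effect sizes or on sphericity; the size of the gain depends on both. The finding does not make the planned rule an error, nor does it show the study to be too small.

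**What to change.** Limit the post-hoc sentence to the stimulus factor and add one for ISI, for example: if the ISI main effect is significant, the three ISI pairs are compared by paired t-tests with the Shaffer step-down procedure (smallest p-value against 0.05/3; if it is rejected, the other two each against 0.05).

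Testing each pair at 0.05 after the omnibus test is an acceptable alternative only if the same sentence requires a Greenhouse-Geisser-corrected omnibus test.

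The cost is a sentence in the plan, with no extra data or participants. It can be made before preregistration, which the protocol places ahead of recruitment. The price is a familywise error within each ANOVA that moves from about 2–4% towards 5%. The rise arises when exactly one pair is equal (about 1.7% to 5%); when all three means are equal, the first step is the same as the plan's and the error is unchanged. As now, nothing adjusts across the ten ANOVAs.
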